## Appendix 4 – Medication adherence questionnaire

| Question                                                                       | Response(s)                                                                                                                                                                                                                                                               |
|--------------------------------------------------------------------------------|---------------------------------------------------------------------------------------------------------------------------------------------------------------------------------------------------------------------------------------------------------------------------|
| Have you been taking the prescribed antibiotics?                               | 
 
• Yes
 
• No
 
                                                                                                                                                                                                     |
| If not taken any antibiotics, what are the reasons?
(Select all that apply) | 
 
• Forgot to fill the prescription
 
• Forgot to start antibiotics
 
• Did not agree with the management prescribed
 
• Worried about side effects
 
• Other (specify)
_____
 
             |
| Have you missed any doses of the antibiotic?                                   | 
 
• Yes
 
• No
 
                                                                                                                                                                                                     |
| Can you estimate how many doses you have missed?                               | 
 
• 1-4 total doses
 
• 5-10 total doses
 
• >10 total doses
 
                                                                                                                                             |
| What were the reasons for missing doses?
(Select all that apply)            | 
 
• Forgot
 
• Experienced side effects
 
• Felt treatment was not working
 
• Confused about frequency of doses
 
• Felt antibiotics no longer required
 
• Other (specify)
_____
 
 |

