#### Feasibility outcomes

Feasibility outcomes assessed will include:

- Eligibility to recruitment ratio
- Retention rate
- Adherence to protocol
- Cross-over from intervention to control group

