### 3.3 Intervention

Patients will receive 2 weeks of antibiotic therapy from date of index X-ray demonstrating no radiological evidence of osteomyelitis.

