### 3.4 Control

Patients will receive 6 weeks of antibiotic therapy from date of index X-ray demonstrating no radiological evidence of osteomyelitis.

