**Figure 1: Study design overview**

### 3.6 Antibiotic choice

Antibiotic choice, including agent, dosing and route of administration, will be at the discretion of treating clinicians based on the results of any relevant microbiological culture and susceptibility results, such as wound swab cultures.

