#### 6.2 Statistical methods to be undertaken

Results will be presented according to CONSORT guidelines for feasibility studies. Data analysis will be conducted on an intention-to-treat principle alongside an additional per-protocol analysis.

Feasibility outcomes will be presented as percentage with 95% confidence intervals. Exploratory clinical outcomes and safety outcome will be presented as risk difference with 95% confidence intervals.

Amount and pattern of missing data will be explored.

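### Appendix 4 bands missed doses without a denominator, so it cannot give the proportion of doses taken, and the cross-over outcome leaves out early stopping in the 6-week arm

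*Protocol*

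**What the plan says.** - **Course length.** Protocol 3.3: "Patients will receive 2 weeks of antibiotic therapy from date of index X-ray". Protocol 3.4: "Patients will receive 6 weeks of antibiotic therapy from date of index X-ray". The synopsis counts both courses from randomisation instead.
- **Dosing.** Protocol 3.6: "Antibiotic choice, including agent, dosing and route of administration, will be at the discretion of treating clinicians". Doses per day are therefore not fixed.
- **Adherence form.** Appendix 4 opens with "Have you been taking the prescribed antibiotics" and later asks "Can you estimate how many doses you have missed". The three answers are absolute counts, such as "5-10 total doses", and are identical in both arms. There is no field for doses prescribed and no stated recall period. Section 3.9 lists the form for the day 14, 42 and 90 assessments.
- **Outcomes.** Section 2.3 makes feasibility part of the primary endpoint. Its list includes protocol adherence, which it does not define further, and "Cross-over from intervention to control group". The synopsis list omits cross-over, and neither list has the reverse direction.
- **Analysis.** Section 6.2: "Feasibility outcomes will be presented as percentage with 95% confidence intervals". It adds a per-protocol analysis beside intention-to-treat.

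**The concern.** A count of missed doses means little without the number due. Ten missed doses are most of a once-daily 2-week course and a small part of a four-times-daily 6-week course, yet both are recorded in the same band. An analysis plan can define adherence as it likes, but it cannot recover a denominator or an exact count that the form never collected.

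Two further gaps concern duration, which is the randomised contrast. A 2-week participant who has stopped as assigned finds no answer at day 42 saying that the course is finished. And separation between the arms shrinks both when 2-week participants continue and when 6-week participants stop early, but only the first is a listed outcome.

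At stake are the adherence and separation figures that a definitive trial would take from this pilot, and a per-protocol set that applies the same standard to both arms.

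**Working it through.** **The plan's own figure.** Section 6.1 gives one number for feasibility outcomes: a confidence interval below 20% with 120 participants. The full Wald width at p = 0.5 is 2 × 1.96 × √(0.25/120) = 17.9%, so the figure reproduces for a pooled percentage. One-way cross-over has only the 60 intervention participants as denominator. There the width is 25.3% at p = 0.5, 20.2% at p = 0.2 or 0.8, and 15.2% at p = 0.1 or 0.9.

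**Inputs.** Courses of 14 and 42 days (3.3, 3.4), a ratio of 3.0 in days. The ratio in doses is the same only at equal dosing frequency. Doses per day (1 to 4), per-dose miss rates (5%, 10%, 20%) and independence of misses are assumptions, since the protocol gives none of them.

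**Step 1: what each band means as a share of prescribed doses** (missed ÷ (doses per day × days)), at 2 doses per day:

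| Band | 2 weeks (28 doses) | 6 weeks (84 doses) |
|---|---|---|
| 1-4 | 3.6-14.3% | 1.2-4.8% |
| 5-10 | 17.9-35.7% | 6.0-11.9% |
| >10 | from 39.3% | from 13.1% |

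Between 1 and 4 doses per day, the top band begins at 78.6% down to 19.6% missed on the 2-week course, and at 26.2% down to 6.5% on the 6-week course. The bands therefore differ in meaning within an arm as well.

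**Step 2: same behaviour, different band.** With n doses due and miss rate q, P(X ≥ 5) = 1 − Σ(k = 0 to 4) C(n,k) q^k (1−q)^(n−k). At 2 doses per day:

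| Miss rate | 2-week course, n = 28 | 6-week course, n = 84 | Days 14-42 only, n = 56 |
|---|---|---|---|
| 5% | 1.2% | 41.1% | 14.7% |
| 10% | 14.2% | 93.1% | 67.1% |

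The last column applies if the day-42 question looks back only to day 14. In an arm of 60, the 5% row means about 60 × 0.012 = 0.7 against 60 × 0.411 = 24.7 participants over the whole course.

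**Step 3: sensitivity to the cut.** P(more than 10 missed), 28 against 84 doses: 0.0% and 0.3% at a 5% miss rate, 0.0% and 21.6% at 10%, 1.5% and 96.3% at 20%. Once daily at 5%, P(X ≥ 5) is 0.04% and 5.7%. The size of the gap depends heavily on the cut, the frequency and the miss rate.

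**Step 4: can the bands support a per-protocol rule?** Take 80% of doses taken as an illustration; the protocol sets no threshold. At 2 doses per day it allows 0.2 × 28 = 5.6 missed doses in 2 weeks, inside the 5-10 band, and 0.2 × 84 = 16.8 in 6 weeks, inside the open >10 band. Participants on both sides of the threshold share a band in each arm.

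**Step 5: day 14.** Both arms have then had the same 14 days of treatment, so course length causes no difference. Only dosing frequency does.

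**The case against.** A reader might infer that two primary outcomes are invalid, or biased between arms. The documents do not support that.

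- Section 6.2 plans percentages with intervals for feasibility outcomes and names risk differences only for clinical and safety outcomes. One-way cross-over is a single-arm measure, so it leaves a direction uncounted but biases no comparison.
- The percentage promised in 6.2 can be one of participants, and the bands do give that. The protocol never promises a proportion of doses taken.
- The protocol-adherence outcome is not tied to the Appendix 4 bands, and its definition may be in an analysis plan that is not shown.

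Nor does the form force a correctly stopped 2-week participant to report non-adherence. The question on reasons is addressed to people who took no antibiotics and has a free-text option. That answer is one reading of loose wording, and by day 90 the ambiguity affects both arms alike.

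It would also be too strong to say that loss of separation goes unmeasured. Section 3.9 collects antibiotic changes at every follow-up in both arms. Section 2.3 lists cross-over out of the 2-week arm, and antibiotics prolonged beyond plan for persistent infection. Some Appendix 4 reasons for missed doses would also reveal early stopping.

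All of this stands, and it limits the point. It does not supply the missing denominator. Appendix 4 is the only dedicated adherence form, and the protocol does not link the record of antibiotic changes to adherence or cross-over.

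**Conclusion.** The point holds as a defect in what is collected. From day 42 on, and for whole-course adherence, Appendix 4 cannot give the proportion of doses taken or classify participants for a per-protocol analysis by the same standard in both arms. At an assumed twice-daily dosing with independent misses, equal behaviour puts 1% against 41% of participants (5% miss rate) or 14% against 93% (10%) at 5 or more missed doses over the whole course. With recall limited to days 14-42, the 6-week figures are 15% and 67%. These figures illustrate the size of the problem and do not predict results, because the protocol fixes neither frequency nor miss rate nor cut-off.

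The form also lacks a planned-completion answer for 2-week participants at day 42, and early stopping in the 6-week arm is not counted as an outcome, though the record of antibiotic changes may partly capture it. This justifies a form and wording change. It does not show that the primary endpoint fails.

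**What to change.** In Appendix 4, replace the three bands with two numbers for the interval since the last visit: doses missed and doses prescribed. Add an answer for a course completed as planned, and record actual antibiotic start and stop dates.

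Report two measures and keep them apart:

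1. The proportion of prescribed doses taken, by arm.
2. Departures from assigned duration in both directions: continuing past the assigned stop in the 2-week arm and stopping early in the 6-week arm. Reword the cross-over item in 2.3 to match.

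Both are needed because a course that the clinician extends or shortens can show full adherence to what was prescribed while departing from the assigned duration.

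Duration needs a single origin. The synopsis (randomisation) and 3.3 and 3.4 (index X-ray) differ and must be reconciled before departures are counted.

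The cost is a form edit, a change of outcome wording and a slightly longer questionnaire. Treatment is unchanged. Answers already collected on the present bands cannot be converted later.
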